- In addition to the difference in surgical method, the two groups will be compared by recording the variables for radiology and clinical surgical outcomes while receiving the identical treatments and follow-up (day of surgery as well as 2 weeks, 3 months, 6 months and 1 year after the surgery). The patients planned to be enrolled in this study will be given an explanation on the objectives and method of the study from the study coordinators before participating, and become enrolled in the study by signing the informed consent form. Screening assignment numbers are assigned as a 6-digit number – the first digit of the randomization number represents the clinical trial site; the second digit represents the sub-study; the third digit represents S in Screening; and the last three digits represent the serial number for enrollment (e.g. B1S-001 -> first screened patient for detailed surgery 1 at Seoul National University Bundang Hospital)

- Among subjects who have agreed to participate in the study voluntarily and have signed the informed consent form, those who meet the inclusion and the exclusion criteria will be randomized to one of the two groups in 1:1 ratio.
- For randomization, the permuted block randomization method will be used. Randomization will be applied to subjects in sequential order starting from Subject no. 1 using iCReaT, a web-based eCRF. The investigator will perform the corresponding surgery depending on the randomization result for each subject. To minimize bias, randomization will be performed by a researcher and the randomization code will be notified to the surgeon immediately prior to the surgery.
- The randomization number is assigned as a series of 5-digit number in which the first digit represents the clinical trial site; the second digit represents the sub-study; and the remaining 3 digits represent the serial number for enrollment (e.g. B1-001 -> first enrolled patient for detailed surgery 1 at Seoul National University Bundang Hospital)
- All basic tests and questionnaires will be conducted at prior to surgery, on the day of surgery as well as at follow-up 2 weeks, 3 months, 6 months and 1 year after the surgery.

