Before surgery, conduct pre-surgery radiological assessment, clinical physical examination (age, gender) and medical history taking (disease history, surgical history) for these subjects, and check the results of the clinical laboratory tests (CBC, Routine chemistry). Check for complications based on radiological imaging tests (X-ray) before surgery, immediately after surgery (X-ray, MRI or CT), and 2 weeks, 3 months, 6 months and 12 months after the surgery. Perform clinical assessments by conducting questionnaires on VAS, ODI, EQ5D, gait, satisfaction, and POSAS before surgery and 2 weeks, 3 months, 6 months and 12 months after the surgery. Immdiately after the surgery, take measurements on the items related to the surgery (postsurgery bleeding, duration of surgery, hospital stay, Creatine Kinase (CK, CPK) at postoperative day 1) to compare surgery-related items.

- However, if the subject is unable to visit the site at planned dates due to unavoidable reasons (such as safety issues due to COVID-19), non-face-to-face treatment or telephone surveys permitted by the current laws can replace the actual outpatient visit.

Eligibility:

Patients with ≥ grade B lumbar central canal stenosis who agree to undergo one to two segment posterior spinal decompression surgery, those who can be followed up for at least 1 year.

Inclusion Criteria:

1. Ages 20 to 80
2. Patients ≥ grade B lumbar central canal stenosis who agree to undergo one to two segment posterior spinal decompression surgery
3. Those who can be followed up for at least 1 year
4. Subjects who signed the informed consent form on own (if the subject is able) or through a legally authorized representative after fully understanding the details of the clinical trial

Exclusion Criteria:

1. Patients with spondylolisthesis (Meyer grade ≥ II)
2. Those who have had the same segmental surgery
3. Degenerative lumbar scoliosis (Cobb angle > 20°)
4. Cause of the lumbar spinal stenosis is not of degenerative nature or it is caused by lumbar disc herniation
5. Presence of other spinal disorders in the lesions of the lumbar spinal stenosis (e.g. ankylosing spondylitis, spinal tumor, spinal fracture)
6. Psychological disorders (such as dementia, intellectual disability, or drug abuse)
7. Those who have refused to participate in the study
8. Other patients deemed ineligible by the investigator to participate in the clinical trial

Treatment Plan:

- Surgical Method

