The surgical method investigated in this study is the most commonly used technique for lumbar spinal stenosis, and the clinical study is conducted through pre- and post-operative surveys and analysis of clinical and imaging data, so there is no harm to the subjects. However, if the subject refuses to participate in the study, the trial will not proceed with the subject. In addition, although this study is conducted on a patient group, there is no obligation or undue influence for participation, and there is no disadvantage to the patient for not participating in the study. Among those who voluntarily agreed to participate in this study and signed an informed consent form (ICF), those who met the inclusion criteria for this study and were not applicable to the exclusion criteria were selected, and subjects were randomly assigned to either of the study or control groups. The Principal Investigator (PI) of this study will not exclude subjects who are likely to participate in this study based solely on race or socioeconomic status. As long as the subject is eligible in terms of inclusion/exclusion criteria, the PI will make every effort to encourage the subjects to participate in the study, and inform the subjects of the objectives of this study so that they can properly represent the total of the patients who will undergo the treatment.

Assessment and Analysis of Study Results and Items for Observation

- **Demographic information:** Age, gender, and date of surgery of subjects

– **Physical examination and basic tests:** Medical history, smoking habits, basic blood tests, physical examination

– **Radiological tests:** The subjects undergo simple radiography and MRI (or CT) examination for baseline assessment. After surgery, during the hospitalization period, the degree of canal release, complications, and recurrence are examined through simple radiography and MRI (or CT) scans.

- **Oswestry disability index (ODI) questionnaire:** Scoring of the Oswestry disability index (10 items) is conducted at the visit. The investigator hands out the subject a questionnaire, and asks the subject to rate each item on a five-point scale for self-report. The rated score is expressed as a percentage of the total score of the answered questions excluding the questions not completed by the subject.

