Statistical analysis method: Equivalency will be declared if the upper and lower limits of the 95% confidence interval (CI) of the treatment difference value of each group’s ODI score at 12 months postoperatively fall within the pre-defined equivalence margin (+-12.8).

1. Secondary Endpoints

The secondary endpoints for this trial include clinical outcomes (VAS, EQ5D-5L, ODI, walking distance and time, satisfaction after surgery, time required to return to daily activities postoperatively, POSAS), radiographic outcomes, and other surgery-related outcomes.

Statistical analysis method: For each group, the differences from the baseline values to the postoperative values and differences in the pattern of change between the two groups are analyzed using repeated measures analysis of variance (ANOVA). In addition, for specific within-group or between-group comparisons at each time point, the t-test is used, while applying the adjusted significance level considering the multiplicity of the test.

Satisfaction after surgery, time required to return to daily activities postoperatively, Patient and Observer Scar Assessment Scale(POSAS scale)

Statistical analysis method: The satisfaction after surgery, the time to return to daily activities postoperatively, and POSAS scale score at the time of final postoperative follow-up are comparatively analyzed between the two groups using the t-test.

- Radiographic outcomes

Examination of the occurrence of complications during the final follow-up using simple radiographs (Development of spondylolisthesis, progression of degenerative lumbar spinal conditions, etc.), analysis of surgical outcomes through postoperative MRI (or CT)

- Statistical analysis method: The occurrence of complications is examined for each group, and Chi- square test or t-test is used for comparative analysis on the difference between the two groups for the degree of central canal release and the canal dimension measured using postoperative MRI or CT.

- Other surgery-related outcomes

Comparison between the two groups on other surgery-related outcomes. [size of the surgical skin incision, postoperative drainage, operative time, duration of hospitalization (hours), Postoperative (From immediately after surgery to discharge from the hospital), postoperative Day 1 creatine kinase (CK, CPK)]

Statistical analysis method: The degree of difference between the two groups is evaluated using the chi-square test or t-test.

General Statistical Analysis

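### Canal release and canal dimension are compared by unadjusted tests that name only the postoperative scan; the scheduled preoperative scan should define release and enter as a covariate

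*Protocol*

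**What the plan says.** In the Protocol, under Secondary Endpoints, the radiographic paragraph states that a "Chi- square test or t-test is used for comparative analysis on the difference between the two groups", and the quantities compared are "the degree of central canal release and the canal dimension measured using postoperative MRI or CT". No change score or baseline covariate is named, and degree of release is not defined anywhere in the document.

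The Radiological tests item, under Assessment and Analysis of Study Results, plans a scan before surgery: "The subjects undergo simple radiography and MRI (or CT) examination for baseline assessment". The next sentence places the assessment of release in the hospital stay: "After surgery, during the hospitalization period, the degree of canal release, complications, and recurrence are examined". The Schedule of Activities agrees, with MRI or CT marked at screening and at the operation visit.

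Inclusion criterion 2 admits "Patients ≥ grade B lumbar central canal stenosis who agree to undergo one to two segment posterior spinal decompression surgery". Severity at entry is therefore open-ended above grade B, and either one or two levels may be operated on.

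**The concern.** Release is a gain: the canal after surgery relative to the canal before it. If only the postoperative canal is measured, a canal widened from 50 to 100 units and one widened from 90 to 100 units (invented figures) both score 100, although the gains are 50 and 10. The entry criterion lets preoperative canal size vary between patients, and the named tests leave whatever part of that variation carries through to the postoperative scan in the error term.

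The imaging outcome is the plan's direct anatomical evidence on whether the endoscopic route opens the canal as fully as open surgery. It is a secondary outcome. The equivalence conclusion rests on the ODI and is not touched by this point.

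**Working it through.** **Inputs.** Allocation is 1:1 ("will be randomized to one of the two groups in 1:1 ratio") with 60 per group. The target includes 20% loss, which would leave 60 × 0.80 = 48, but that loss is follow-up loss. The release scan is taken in hospital, so 60 is the relevant base. The protocol gives no sample size, SD or effect size for the canal outcome, so it has no figure of its own to reproduce here. The correlation r between preoperative and postoperative dimension is also not given. I assume r = 0.3, 0.5 and 0.7, with equal SDs before and after.

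**Step 1: is the unadjusted comparison biased?** Simulation of 20,000 trials per value of r, 60 per arm, no treatment effect, t-test on the postoperative value. The mean between-arm difference was within 0.001 SD of zero. Type I error was 4.9%, 4.7% and 5.2% at r = 0.3, 0.5 and 0.7. There is no systematic bias.

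**Step 2: what precision is given up?** Relative to the postoperative-only comparison (variance 1):
- ANCOVA on the preoperative value: v = 1 − r² (ignoring the one degree of freedom spent).
- Plain change score: v = 2(1 − r).
- Equivalent n per group under ANCOVA: 60/(1 − r²).
- Power for a difference of 0.5 SD (an illustrative size): Φ(0.5/(√(2/60)·√v) − 1.96), with √(2/60) = 0.183. With v = 1 this is 78%.

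| r | ANCOVA variance | Equivalent n per group | Power, ANCOVA | Change-score variance | Power, change score |
|---|---|---|---|---|---|
| 0.3 | 0.91 | 60/0.91 = 66 | 82% | 1.4 | 64% |
| 0.5 | 0.75 | 60/0.75 = 80 | 89% | 1.0 | 78% |
| 0.7 | 0.51 | 60/0.51 = 118 | 97% | 0.6 | 94% |

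A plain change score does worse than the postoperative value alone when r is below 0.5, so the between-arm comparison should be ANCOVA and not a t-test on change.

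**Step 3: how large can chance imbalance be?** The standard error of the baseline difference between arms is √(2/60) = 0.183 SD, so its 95% range is ±1.96 × 0.183 = ±0.36 SD. At the edge of that range the unadjusted result shifts by r × 0.36, which is 0.11, 0.18 or 0.25 SD. In the simulation, among the 5% of trials with the largest imbalance in one direction, type I error without adjustment was 8%, 15% and 23%.

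**Step 4: does the postoperative value stand in for release in a patient?** Its correlation with the true change is √((1 − r)/2), which is 0.59, 0.50 and 0.39. It is a weak proxy.

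**The case against.** Four objections carry weight.

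*The text does not say that release comes from the postoperative scan alone.* A reader might infer this, but the documents do not establish it. Release and canal dimension are listed as two variables, the phrase about the postoperative scan may qualify only the second, and a t-test or chi-square test could be applied to a change or to a graded reading. This stands. The point is therefore limited to what is written: only the postoperative scan is named, and the tests carry no baseline term. For canal dimension that is explicit. For release, no derivation is stated.

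*The general method for secondary endpoints covers it.* That paragraph lists radiographic outcomes and then describes analysing "the differences from the baseline values to the postoperative values and differences in the pattern of change between the two groups" by repeated measures ANOVA. The radiographic paragraph, however, names its own, different tests. At the least, the two need to be aligned.

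*Definitions and covariates belong in the SAP.* The SAP is not shown and may define release. The protocol has nevertheless named the scan and the tests, so the comment concerns a stated method.

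*Randomization already takes care of it.* For bias, this is correct: both analyses estimate the same expected contrast, and the t-test's standard error already allows for chance imbalance on average. What remains is efficiency, and the conditional error in trials that happen to be imbalanced.

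**Conclusion.** The point holds as a minor improvement to one secondary endpoint. The protocol names unadjusted tests and only the postoperative scan, while a preoperative scan is scheduled and its use is not stated. A reader might go further and conclude that patients with wider canals at entry distort the comparison in favour of one arm. The documents do not support that: allocation is randomized, and the check shows no bias and type I error close to 5%.

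The size of the loss depends on an unknown correlation. Over r = 0.3 to 0.7, ANCOVA would remove 9% to 49% of the variance. At r = 0.3 the gain is modest (power 78% to 82% for a 0.5 SD difference). These figures assume equal SDs, 60 measurable patients per group and a continuous dimension. They do not carry over to a graded reading.

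**What to change.** In the radiographic paragraph under Secondary Endpoints:

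- Define degree of release from paired preoperative and postoperative scans at the operated level or levels, and state how a two-segment patient yields one value (for example, the mean over operated levels).
- Compare the arms by ANCOVA of the postoperative dimension on the preoperative dimension. For a graded reading, compare the postoperative grade adjusted for the preoperative grade. Report the change descriptively.
- Since MRI or CT is allowed at each time, use same-modality pairs, or add modality as a covariate where the two are mixed.
- State that this paragraph replaces the general repeated measures method for these outcomes.

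The cost is a few sentences, measurement of preoperative scans that are already taken, and a missing-data rule for patients without a measurable one. No additional imaging is needed.

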- **EQ5D-5L questionnaire:** The EQ5D-5L questionnaire (5 items) is conducted at the visit. The investigator hands out the subject a questionnaire and asks the subjects to rate and indicate each item for self-report. The total score of the indicated items is converted using the EQ5D value set for calculation.

- **VAS score ( pain scale):** The degree of pain felt by the subject during activity is assessed using a 100mm VAS (Visual Analogue Scale) for both lower back and the legs. The investigator explains the VAS to the subject and asks the subject to rate each item and indicate accordingly for self-report. In addition, the degree of pain in the surgical site (Postoperative Day 1 or Day 2) is also investigated using VAS.
- **Walking time:** The changes in values in the questions on walking ​​at postoperative 2, 12, 24, and 52 weeks are compared to the baseline values.
- **Satisfaction after surgery:** At the 1-year follow-up visit, the investigator hands out the questionnaire to the subject and asks the subjects to indicate for self-report.
- **Return to daily activities after surgery:** The time required to return to daily activities postoperatively (week)
- **Scar after surgery (POSAS[Patient and Observer Scar Assessment Scale] patient scale 2.0):** The patient assesses the postoperative scarring with 6 items and scored on a ten-point system, with a score of 1 indicative of normal skin and a score of 10 indicative of the worst scar imaginable, and the total score of the assessment is 60.

- **Other surgery-related outcomes:** The size of the surgical skin incision, postoperative drainage, operative time, duration of hospitalization (hours), postoperative Day 1 creatine kinase (CK, CPK) are also evaluated.

- **Presence of adverse events and complications:** Adverse events requiring revision surgery related to the intervention. When a patient arrives at the ward after completing the surgery, a resident (or fellow, clinical instructor, nurse, investigator, etc.) who is blinded to the surgical method examines the patient to determine whether there are any complications related to the intervention or any serious complications that require revision surgery.

Efficacy Assessment Criteria, Assessment Method, Interpretation

1. Primary Endpoint

The primary endpoint of this trial is the difference between the ODI score measured at baseline and that measured 12 months postoperatively.

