| --- | --- | --- | --- | --- | --- | --- |
| **Patient Evaluation:**  **Schedule of Activities** | | | | | | |
| **Visit Type** | **Screening** | **Operation/**  **Treatment** | **Follow-up** | | | |
| **Visit** | **1** | **2** | **3** | **4** | **5** | **6** |
| **Visit week** | **-4~0weeks** | **0 day** | **2 weeks** | **12 weeks** | **24 weeks** | **52 weeks** |
|  |  |  | **± 5 days** | **± 4 weeks** | **± 8 weeks** | **± 8 weeks** |
| Subject written consent | ■ |  |  |  |  |  |
| Demographic information | ■ |  |  |  |  |  |
| Medical history/Surgical history^[1]^ | ■ |  |  |  |  |  |
| Physical examination | ■ |  |  |  |  |  |
| Clinical laboratory tests^[2]^ | ■ |  |  |  |  |  |

| Inclusion/Exclusion criteria | ■ | ■ |  |  |  |  |
| --- | --- | --- | --- | --- | --- | --- |
| Randomization |  | ■ |  |  |  |  |
| Surgery |  | ■ |  |  |  |  |
| MRI or CT | ■ | ■ |  |  |  |  |
| X-ray^[4]^ | ■ |  | ■ | ■ | ■ | ■ |
| ODI questionnaire | ■ |  | ■ | ■ | ■ | ■ |
| EQ-5D questionnaire | ■ |  | ■ | ■ | ■ | ■ |
| VAS questionnaire | ■ |  | ■ | ■ | ■ | ■ |
| Walking questionnaire |  |  | ■ | ■ | ■ | ■ |
| Other questionnaire^[5]^ |  |  | ■ | ■ | ■ | ■ |
| Collection of adverse events |  | ■ | ■ | ■ | ■ | ■ |
| * Visit 1 and visit 2 may proceed concurrently.   1. Investigation of medical history within 3 years from the time of screening (5 years in case of cancer) 2. Laboratory tests:   - Hematology (CBC): WBC, Hb, Hct, ESR - Biochemical profile (routine chemistry): hs-CRP, CPK   1. Simple radiography (X-ray): Simple radiographs will be obtained in the anteroposterior (AP), lateral, lateral-flexion, and lateral-extension views. In order to prevent undergoing excessive radiographic examinations, it is possible to replace the examination results with those taken within 4 weeks from the date of screening or follow-up visit. 2. Other questionnaires: satisfaction with the surgery, daily activities, POSAS scar questionnaire | | | | | | |

Expected Adverse Events/Risks and Countermeasures

The posterior spinal decompression surgery to be performed in this trial is a standard treatment for patients with lumbar spinal stenosis. There are no additional complications specifically from this study other than those related to general spinal surgery.

However, if AEs related to this clinical study occur, the investigator will take the following actions:

1. The investigator will immediately report to the IRB upon discovering the adverse event.

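### The Day 1 creatine kinase comparison names no use of the preoperative CPK already collected, which gives up precision on one secondary outcome

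*Protocol*

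**What the plan says.** Day 1 CK is a secondary outcome. The protocol's list of items for observation says that "postoperative Day 1 creatine kinase (CK, CPK) are also evaluated". Under Secondary Endpoints, the subsection on other surgery-related outcomes groups it with incision size, drainage, operative time and hospital stay, and gives the group one rule: "The degree of difference between the two groups is evaluated using the chi-square test or t-test". No covariate and no measurement scale is named.

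A preoperative value of the same enzyme is collected. The Schedule of Activities ticks clinical laboratory tests at screening, and its footnote gives the panel as "Biochemical profile (routine chemistry): hs-CRP, CPK". The Study design section agrees: before surgery, staff are to "check the results of the clinical laboratory tests (CBC, Routine chemistry)".

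The purpose given for the postoperative sample is short: "Creatine Kinase (CK, CPK) at postoperative day 1) to compare surgery-related items".

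One further sentence bears on the point. Near the top of Secondary Endpoints, a general method sentence runs in part "the differences from the baseline values to the postoperative values and differences in the pattern of change between the two groups are analyzed using repeated", and the model it goes on to name is a repeated measures ANOVA. The endpoint list just above that sentence includes the other surgery-related outcomes.

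**The concern.** When a preoperative measurement of the outcome exists, a two-sample test on the postoperative value alone leaves between-patient variation in the error term that the baseline could remove. The protocol does more than stay silent here. It names a test for this group of outcomes, and the test does not use the baseline. A plan that follows the protocol literally would inherit the unadjusted comparison.

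The chi-square alternative adds a small looseness. CK is continuous, so chi-square could apply only after a cut-point is chosen, and none is given.

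CK matters somewhat because it does not depend on self-report. The protocol accepts that patients will know their procedure from the incision site, which exposes questionnaire outcomes to that knowledge but not a laboratory value. The rationale also cites loss of paraspinal muscle as a problem of conventional surgery. Linking CK to that claim is an inference, because the protocol does not make the link itself. At stake is the chance of detecting a real CK difference and the width of its confidence interval.

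**Working it through.** **Which rule governs CK.** There are two candidates: the specific chi-square or t-test rule, and the general repeated measures sentence on change from baseline. The other surgery-related outcomes have their own subsection and method, so the specific rule is the natural reading. The general sentence overlaps through the endpoint list but does not clearly govern CK. If it was meant to, CK has two methods and a line is still needed to settle it.

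**Inputs from the protocol.** 1:1 allocation and 60 per group. The 60 was set for the ODI: 2 × (18.8 × (1.645 + 1.645) / 12.8)² = 46.7, so 47, and 47 / 0.80 = 58.75, so 59, using one-sided 0.05 per test. No figure is stated for CK, so there is none to reproduce. I take 60 per arm as the CK sample size, because the 20% loss is an allowance for follow-up to the 1-year ODI and the CK sample is drawn the day after surgery.

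**Inputs assumed.** The protocol gives no SD, skewness, baseline correlation r or expected treatment ratio for CK. Ranges are shown instead.

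**Step 1: validity.** With log-normal CK, 60 per arm, no treatment effect and 10,000 replicates, the raw-scale t-test rejected in 0.041 to 0.052 of trials over log-SD 0.5 to 1.0. Type I error is sound even under marked skew.

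**Step 2: gain from baseline adjustment.** The variance of the ANCOVA estimate relative to the unadjusted one is 1 − r². For an effect at which the unadjusted test has 80% power, power after adjustment is Φ((1.960 + 0.842)/√(1 − r²) − 1.960).

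| r | 1 − r² | Variance cut | SE cut | 80% power becomes |
|---|---|---|---|---|
| 0 | 1.00 | 0% | 0% | 80% |
| 0.3 | 0.91 | 9% | 5% | 84% |
| 0.5 | 0.75 | 25% | 13% | 90% |
| 0.7 | 0.51 | 49% | 29% | 97% |

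**Step 3: gain from the log scale, if CK is right-skewed.** Simulation with 60 per arm, log-normal CK, true ratio 1.5, 35% two-segment cases with a log effect of 0.3 (all assumed), two-sided 0.05 and 4,000 replicates. The ANCOVA column adjusts for baseline and segments, over r = 0.3 to 0.6.

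| log-SD | Raw t-test | Log t-test | Log ANCOVA |
|---|---|---|---|
| 0.6 | 90% | 95% | 97-99% |
| 0.8 | 65-66% | 77-78% | 82-92% |
| 1.0 | 42-44% | 59-61% | 64-79% |

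The Monte Carlo standard error is at most √(0.5 × 0.5 / 4,000) = 0.8 points per entry. The log scale alone adds about 5 to 18 points. Number of segments contributes at most about 1 to 2 points, so baseline and scale drive the gain. At r = 0 and log-SD 0.8, log t-test and log ANCOVA both give 77-78%, so an uninformative baseline costs essentially nothing.

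**Step 4: a different assumed effect.** With ratio 1.4, no segment effect and r = 0.5, power for raw t, log t and log ANCOVA is 93%, 96% and 99% at log-SD 0.5; 50%, 63% and 75% at 0.8; and 31%, 45% and 55% at 1.0. The ordering holds, but at log-SD 0.5 the differences are small.

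**The case against.** The strongest objection is that this is a preference about efficiency. Transformation and covariates for one laboratory item are ordinary SAP content, the SAP is not shown, and nothing in the protocol forbids a log scale. The part about scale stands: a reader might infer that CK will be analysed untransformed, but no scale is stated. What remains is that the protocol does name a test for this outcome, and the named test leaves out a baseline that the trial collects.

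A reader might also infer that the preoperative CPK is ruled out of the analysis. That goes too far, because the general repeated measures sentence overlaps. The supportable statement is that no use of it is clearly specified.

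A third tempting reading is that high preoperative CK or two-segment surgery falling by chance in one arm could produce a spurious difference. Under 1:1 randomisation that is ordinary chance imbalance, already counted in the significance level, and Step 1 bears this out.

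On chi-square, the sentence covers a list and can be read as whichever test suits the variable. Nothing says CK will be dichotomised, so this is a matter of tidiness.

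Finally, skewness and baseline dependence of CK are not in the documents, and General Statistical Analysis already calls for median, minimum and maximum, so marked skew would be visible. This is why the gain is given as a range that starts at zero.

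**Conclusion.** The point holds as a minor matter of efficiency. The protocol names an unadjusted test for Day 1 CK and no clear use of a preoperative CPK that it already collects. The comparison remains unbiased with valid type I error. The cost is precision: none at r = 0, 9% of variance at 0.3, 25% at 0.5 and 49% at 0.7, with a further loss if CK is right-skewed and analysed on the raw scale. All these sizes rest on assumed values of r, log-SD and treatment ratio.

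A reader might conclude that the trial's evidence on tissue damage turns on this test. The documents do not support that. CK is one unranked secondary item, the protocol never calls it a marker of muscle injury, and neither the ODI equivalence decision nor the sample size depends on it.

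**What to change.** In the subsection on other surgery-related outcomes, give CK its own sentence: log-transformed Day 1 CK is compared between groups by ANCOVA with log screening CPK as covariate, and the result is reported as a geometric mean ratio with 95% CI. Number of operated segments (one or two) may be added, but is optional given its small contribution. Drop the chi-square option for CK, and state that this sentence, not the general repeated measures method, governs CK. Settle this before outcome data are examined, and carry the same wording into the SAP.

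The cost is one sentence and no new blood sample, since CPK is already drawn at screening. The downside is that the result is a ratio rather than a difference in raw units. Raw-scale medians and ranges can stand beside it, as the protocol's descriptive statistics already provide.
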